### Study procedures and follow‐up

2.3

Upon enrollment, participants are randomly assigned to either the smartphone‐enabled HBET or usual care arm and followed prospectively for 12 weeks. Regardless of the treatment arm, all subjects receive a Fitbit Charge 2 (Fitbit, San Francisco, California) to record various measures of physical activity including steps, exercise activity, and heart rate (HR). All participants are then prescribed an exercise plan according to their study arm as outlined below.

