#### Standard exercise therapy

2.3.1

Patients randomized to the usual care arm receive counseling by their physician to perform self‐monitored walking exercise according to established practice guidelines for PAD. This represents current standard practice at Grady Memorial Hospital and includes a recommendation to perform between 30‐ and 45‐minutes walking exercise three times per week. This is based on prior meta‐analyses which have found that walking at least 30 minutes is more beneficial than shorter durations, and that benefit appears to peak at 45 minutes.^9^, ^30^, ^31^ Participants are instructed to walk at an intensity that induces onset of claudication within 3 to 5 minutes and moderate to moderately severe claudication within 8 to 10 minutes, at which point they should stop and rest until their claudication subsides. After their symptoms dissipate, they should resume this same cycle of exercise until their target exercise duration is reached. In addition to exercise, participants in the standard exercise group receive counseling on healthy lifestyle behaviors including dietary changes, medication adherence, and smoking cessation if needed.

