#### Smartphone‐enabled exercise therapy

2.3.2

Patients in the smartphone‐enabled arm receive an app (Movn, Moving Analytics, Los Angeles, California) to guide their exercise program in addition to the fitness tracker which also synchronizes with the app. Our study team has successfully piloted the use of Movn in the delivery of home‐based CR to veterans with ischemic heart disease.^25^ Movn is a commercially available home‐based exercise rehabilitation program based on the MULTIFIT,^32^ a case‐management system for secondary prevention and patient surveillance after acute MI developed by investigators at Stanford University School of Medicine and implemented within Kaiser Permanente of Northern California. In previous studies, MULTIFIT has been shown to significantly improve low‐density lipoprotein cholesterol (LDL‐C) levels, functional capacity, and rates of smoking cessation after 12 weeks of enrollment compared to usual care.^32^, ^33^ Movn provides virtual delivery of MULTIFIT through a patient‐facing smartphone app that synchronizes with a provider‐facing online case‐management dashboard to allow for remote monitoring of participants' progress (Figure 2). The app includes a virtual diary for participants to enter data on exercise sessions (including exercise time, frequency and symptoms), blood pressure (BP), HR, weight and medication adherence, as well as provide exercise reminder notifications, educational material on heart and vascular health, and two‐way secure messaging with a health coach. The coach is an exercise physiologist with extensive experience in remote coaching (via INTERVENT, Savannah, Georgia). The initial coaching session occurs via video conference and subsequent sessions are performed with brief telephone calls lasting approximately 15 minutes in duration. Customized education modules designed by INTERVENT are used to specifically educate the participants on PAD. The coach facilitates each participant's exercise program by remotely monitoring their progress via the dashboard and providing feedback during scheduled telephone calls occurring at 1 to 2‐week intervals. Participants in the smartphone‐enabled arm receive the same educational topics and guideline‐directed exercise prescription as for the standard exercise arm.

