#### Statistical analysis

2.5.3

For analyses involving comparisons of groups we will perform two‐sample, independent *t*‐tests for normally distributed data, and logarithmic transformations for positive skewed distributions. For highly skewed data where log transformation does not adequately correct the skew, we will use non‐parametric rank‐order tests such as the Wilcoxon rank sum. For between‐group differences, 95% confidence intervals will be constructed, and multivariable adjustments using linear regression will be used where large group imbalances exist. Analyses will be performed as intention‐to‐treat, but we will also do sub‐group analyses based on the degree of engagement with the program. Multiple imputations will be used for missing data using established methods,^44^ and per‐protocol analyses will also be conducted. The a priori level for statistical significance was a two‐sided *P* < .05.

There are no sub‐studies planned, but we will perform predefined subgroup analyses to explore efficacy according to several baseline characteristics including age, ABI results, functional status, revascularization history, and degree of engagement with the smartphone app and coaching program.

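### Degree of engagement is listed as a baseline subgroup for efficacy, but it arises after randomisation, exists only in the HBET arm and is itself a secondary outcome

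*Protocol article*

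**What the plan says.** Section 2.5.3 (Statistical analysis) brings in engagement twice.

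- Next to the intention-to-treat commitment, it adds sub-group "analyses based on the degree of engagement with the program".
- In its last paragraph it says "we will perform predefined subgroup analyses to explore efficacy according to" a list given as "several baseline characteristics including age, ABI results, functional status, revascularization history, and degree of engagement with the smartphone app and coaching program".

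Other sections fix what engagement can mean.

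- **Smartphone arm (2.3.2).** Participants in this "arm receive an app (Movn, Moving Analytics, Los Angeles, California) to guide their exercise program". On coaching: "The coach facilitates each participant's exercise program by remotely monitoring their progress via the dashboard and providing feedback during scheduled telephone calls".
- **Control arm (2.3.1).** "Patients randomized to the usual care arm receive counseling by their physician to perform" walking exercise on their own. No app or coach is described.
- **Both arms (2.3).** The shared tool is the activity tracker: "all subjects receive a Fitbit Charge 2 (Fitbit, San Francisco, California").
- **Outcomes (2.4 and 2.5.1).** Engagement with the app is named as a secondary outcome, in 2.4 together with the coaching program.

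**The concern.** A subgroup analysis of efficacy compares the randomised arms within each level of a factor. For that comparison to keep the protection of randomisation, the factor must be fixed before allocation and defined in both arms. Age, ABI, functional status and revascularization history at entry meet both conditions. Engagement with the trial app and coach meets neither.

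Participants who engage more may be fitter, more motivated or already improving. They could then show a larger 6MWT gain even if the program did nothing. The article does not show that this happens, but nothing in the planned analysis would separate it from a treatment effect.

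The trial is meant to supply evidence for going on to larger efficacy trials (section 1.2). If the intention-to-treat result is null or unclear, a statement that the program works in those who use it is a natural fallback. Calling the analysis a predefined subgroup on a baseline characteristic would give that statement more weight than the design can support.

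**Working it through.** **1. Timing and arm.**

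| Property a subgroup factor needs | Engagement in this article |
|---|---|
| Fixed before allocation | No. Exercise plans are given by arm after assignment (2.3); the app and coaching belong to the smartphone program (2.3.2) |
| Defined in both arms | No. Usual care is physician counselling (2.3.1) |
| Not an outcome of the trial | No. It is a secondary outcome (2.4, 2.5.1) |

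The Fitbit is common to both arms, but section 2.5.3 names the app and the coaching program, not tracker use.

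**2. Feasible contrasts.** Controls have no level of engagement, so two contrasts remain:

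- (a) engaged HBET participants against all controls;
- (b) high against low engagers within HBET.

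Section 2.5.3 does not say which is meant. Both select on behaviour after randomisation. The methods it lists (t-tests, rank tests, regression adjustment for imbalance) do not restore a randomised comparison.

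**3. The article's own design figures.** These are not in dispute; they supply the SD and sample size used below. Using the normal approximation, power = Φ(d·√(n/2) − 1.96):

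- n = 25 per group, d = 0.96: 0.96 × √12.5 = 3.394, and Φ(1.434) = 92.4%. With d = 55/57 it is 92.7%. Stated: 93%.
- n = 17 per group (50 × 0.68 = 34): 79.9% to 80.3%. Stated: 80%.
- Minimum detectable difference: 57 × √(2/25) × (1.960 + 0.842) = 45.2 m. Stated: 45 m.

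**4. Illustration of the selection bias.**

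Inputs from the article: SD of change 57 m, 25 per arm, two-sided 5% level (2.5.2, 2.5.3); small and moderate MCID 11 m and 28 m (2.4.1).

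Assumptions not in the article: no true treatment effect; full retention; engagement split at its median; and a correlation r between engagement and the walking change that the participant would have had anyway.

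For contrast (a), expected false gain = 57 × r × k, where k is the mean standardised engagement of the selected group. For the top 13 of 25 normal values, k = 0.742. The rejection rates come from simulated trials (20,000 or more per value of r) of a two-sample t-test, 13 against 25.

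| Assumed r | 57 × r × 0.742 | Rejection at nominal 5% |
|---|---|---|
| 0 | 0 m | about 5% |
| 0.1 | 4.2 m | about 5.5% |
| 0.2 | 8.5 m | about 7% |
| 0.3 | 12.7 m | about 10% |
| 0.5 | 21.2 m | about 19% |

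The false gain reaches the 11 m small MCID at r = 11 / (57 × 0.742) = 0.26. Taking the top 12 instead of 13 gives slightly larger values: about 9, 14 and 23 m at r = 0.2, 0.3 and 0.5.

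For contrast (b), 12 against 13 within HBET, the false difference is about 18, 26 and 44 m at r = 0.2, 0.3 and 0.5, with rejection rates of about 11%, 20% and 53%. Moving to a within-arm test therefore does not make the result interpretable as efficacy.

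**The case against.** **The sentence may be loosely built.** It can be read as baseline characteristics and, in addition, engagement. That would soften the mislabelling. It would not give controls an engagement level, and the sentence would still promise efficacy by engagement, as does the separate mention beside intention-to-treat.

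**Other places might suggest engagement is available earlier or in both arms.** Table 2 marks app and Fitbit usage at baseline, and the abstract mentions the app without naming an arm. Section 2.3.2 settles this: the app belongs to the smartphone program, and use of it cannot precede allocation.

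**The analysis is exploratory and supplementary.** This stands. The article sets engagement beside the intention-to-treat analysis and uses the language of exploration. The primary estimate, alpha, sample size and power are untouched, which limits the severity.

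**The bias figures rest on an assumed correlation.** This also stands. At r = 0 there is no bias, and below about 0.26 the false gain in contrast (a) is under the small MCID. That engaged participants would have done better anyway is plausible, but the article does not show it.

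**A reader might infer that the plan commits to comparing engagers with controls, or that this is the only comparison possible.** The article does not support either reading. It names no contrast, and a within-HBET comparison is equally open. The point does not depend on which was meant, since neither is randomised.

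**Conclusion.** The point holds: as written, section 2.5.3 puts a variable that arises after randomisation, in one arm only, among the baseline factors for efficacy subgroups, and nothing elsewhere in the article corrects it. This structural conclusion needs no numerical assumption.

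The size is uncertain. Over assumed correlations of 0 to 0.5, the false gain over controls runs from 0 to about 21 m and the false-positive rate from about 5% to 19%, given no true effect, SD 57 m, 25 per arm and a median split.

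A reader might go further and conclude that the trial's main result is biased, or that a clinically important false effect is to be expected. The article supports neither. The primary analysis is by intention to treat, and no correlation is given. The correction should be made before analysis, but it is not a defect in the primary analysis.

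**What to change.** In section 2.5.3, remove degree of engagement from the list of baseline subgroup characteristics. In both places where engagement appears, state that it will be reported only as a descriptive, non-randomised association with 6MWT change within the HBET arm, and not as a subgroup estimate of efficacy.

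The cost is wording only, with no new data, visits or participants. What is given up is an efficacy-by-engagement claim that the design cannot support.

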## RESULTS

3

As of December 15, 2019, a total of 35 patients have been screened and 15 participants have been enrolled and randomized. No significant differences were found between screened and enrolled participants. To date, 13 have completed the study (eight in the treatment group and seven in the control group). See Figure S1 in the Supplementary Appendix. Among all enrolled patients, the mean (SD) age was 66.1 (5.8) years, 9 (60%) were women, and 13 (87%) were black (Table 3). The mean (SD) ABI is 0.86 (0.29), reported as the worst diseased extremity. The baseline 6MWT distance among all participants was 363.5 m. As expected in PAD patients, there was a high prevalence of concomitant hypertension and dyslipidemia. Overall, the prevalence of coronary artery disease (CAD) was lower than expected at 26.7%. The population was well‐treated, however, with 73.3% of patients prescribed both an aspirin and statin.

**TABLE 3 clc23362-tbl-0003:** Baseline characteristics

Characteristic	N = 15
Age	66.1 (5.8)
Female	9 (60)
BMI	29.5 (5.9)
Current smoker	10 (66.7)
ABI	0.86 (0.29)
6MWT distance	363.5 (113.0)
Race	
Black or African American	13 (86.7)
White	2 (13.3)
Comorbidities	
Hypertension	13 (86.7)
Dyslipidemia	12 (80.0)
Diabetes mellitus	8 (53.3)
CAD	4 (26.7)
Chronic systolic HF	2 (13.3)
CVA or TIA	2 (13.3)
History of PCI	3 (0.20)
Medication	
Aspirin	11 (73.3)
Plavix	2 (13.3)
Statin	11 (73.3)
ACE or ARB	9 (60)
Beta‐blocker	7 (46.7)

*Note*: Values are N (%) or mean (SD).

Abbreviations: ABI, ankle‐brachial index; ACE, angiotensin‐converting enzyme; ARB, angiotensin‐receptor blocker; BMI, body mass index; CAD, coronary artery disease; CVA, cerebrovascular accident; HF, heart failure; PCI, percutaneous coronary intervention; TIA, transient ischemic attack; 6MWT, 6‐minute walking test.

## DISCUSSION

4

The Smart Step Study was designed to answer an important question in the management of PAD patients: what the feasibility of a smartphone‐enabled program of remote exercise is to improve functional capacity in patients with claudication receiving care in a low resource healthcare setting. Although several studies are currently underway examining the role of smartphones in PAD management,^23^, ^45^ to our knowledge, the Smart Step study is the first study to evaluate a smartphone‐enabled HBET program in a low resource, public‐hospital setting with a majority of African American patients. The Smart Step trial also integrates a contemporary wearable activity monitor with the Fitbit Charge 2 which will complement that of several other trials which assessed the value of mobile technologies in the evaluation and management of symptomatic PAD.^17^, ^18^, ^19^, ^43^

The Smart Step Study is unique because it primarily targets patients with lower socioeconomic status (SES) in an inner‐city hospital. Although SET program availability is limited in general, PAD patients in underserved populations may have an even higher risk of poor outcomes due to lack of adequate insurance and reliance on lower‐resource healthcare systems without available SET programs. This increases the potential impact of Smart Step to fill a vital gap in care for such individuals, of which large numbers exist and healthcare costs are high. Additionally, since many lower income adults rely on a smartphone to access the internet, the program will likely be feasible in this group as well.^20^

Given the rising prevalence of PAD and the limited availability of supervised exercise, particularly in low resource settings, there is a mounting public health need to develop inexpensive, portable, and scalable SET delivery methods. Despite the substantial benefits associated with supervised treadmill walking,^8^, ^46^ many physicians do not recommend SET to patients with PAD and, even when referred, most eligible individuals do not enroll due to limited availability, lack of insurer coverage, and difficulty with transportation. In combination, these factors make participation in SET burdensome and impractical. The recent availability of smartphones and the proven feasibility of Movn, a smartphone‐enabled home‐based cardiac rehabilitation program, has led to new opportunities to address limitations of SET in a low resource environment with a modified version of the program tailored specifically for PAD.

The smartphone program specifically has several hallmark components that present an evolution in home‐based therapy. First, it automates the data transfer of physical activity (steps, flights of stairs, active minutes) from the patient to the provider, who views the data using a secured online dashboard. Furthermore, it serves as an electronic diary for the patient to record various activities, including medication use, smoking, and exercise sessions—all data are shared with the coach and allow the patient to both reflect on his/her own activity, as well as be accountable to the coach. The patient can also message the coach through the app (between phone sessions), which improves access to care. Coaches can be alerted to patients who have not logged exercise for an extended period, allowing for earlier detection of non‐compliance. Furthermore, the program is integrated with various wearable devices, which potentially allow for sharing HR, among other physiologic data. Education and surveys can also be delivered via the app and organized in the patient's electronic profile.

Prior studies of HBET using mobile technologies have primarily integrated wearable activity monitors as opposed to smartphones and have yielded conflicting results.^17^, ^18^, ^19^ Two early trials by Gardner et al demonstrated high rates of adherence with a quantified home exercise program using a step activity monitor that resulted in significant improvements in claudication symptoms and walking parameters similar to a supervised program.^17^, ^18^ In an early trial, 119 participants were randomized to HBET with an ankle‐mounted step activity monitor (StepWatch 3, Cyma Inc.), traditional supervised treadmill exercise, or usual care. Participants in the HBET group were instructed to exercise in a manner similar to a supervised program. After 12 weeks, both the HBET and supervised exercise groups significantly increased their claudication onset and peak walking times (COT and PWT, respectively) vs usual care. These findings were replicated in the subsequent NEXT Step Study by Gardner et al in 2014 that randomized 180 patients in a similar manner to either HBET, supervised exercise, or attention control.^18^ After 12‐weeks, participants in the home‐based program again demonstrated significant improvements in both COT (*P* < .001) and PWT (*P* < .001) as well as exercise capacity measured by 6‐MWT distance (*P* = .028) compared to usual care. Participants in the home‐based arm performed significantly more exercise measured in terms of total time (1011 vs 762 minutes; *P* = .009) and time per exercise session (38.3 vs 24.7 minutes; *P* < .001) despite a lack of direct supervision.

In contrast, the more recent HONOR Trial by McDermott et al of an HBET intervention using a waist‐worn pedometer (Fitbit Zip) yielded substantially different results. In HONOR, 200 patients with symptomatic PAD were randomized to HBET or to usual care with walking advice only.^19^ Participants in the home‐exercise group completed 12‐weeks of exercise, initially with weekly sessions at the hospital for 4 weeks followed by 8 weeks of completely home‐based exercise with telephone coaching and with the wearable monitor. After 9 months of follow‐up, there was no significant difference in 6‐minute walk distance between the home‐based intervention and usual care group with a surprising trend towards better performance among participants in the usual care group who did not receive exercise coaching (5.5 vs 14.4 m; 95% CI, −26.0 to 8.2; *P* = .31). Total step counts from the Fitbit's accelerometer did not statistically differ between the two groups.

The Smart Step Study offers several important additions to these and other prior HBET studies. First, whereas prior studies have used passive activity trackers such as pedometers and actigraphs only, the use of a smartphone app to enable self‐management and provide clinical support is a novel addition which has only been recently explored in PAD management,^23^, ^45^ and to our knowledge has not been previously deployed in a low‐resource hospital setting. The addition of Movn and INTERVENT also offer novel additions in smartphone‐based delivery and coach training. The study coach underwent rigorous coach training by INTERVENT which has extensive experience in behaviorally‐oriented telephonic health coaching in patients with ischemic heart disease and stroke.^47^

## CONCLUSION

5

Access to a structured exercise walking program is of paramount importance to patients with PAD; however, the multiple barriers including limited availability, inconvenience, and cost has made delivery of facility‐based SET programs challenging. A smartphone‐enabled HBET program, if effective, could have far‐reaching implications for the growing number of PAD patients especially in lower resource settings where participation in SET is virtually nonexistent.
